### Control group

The households in the control arm will receive the waste segregation information dissemination campaign conducted by Ujjain Municipal Corporation, which is routine and same across the city.

In addition, all the participating households (Intervention and control arm) will be provided with a pair of dustbins to enable waste segregation practice.

### Intervention (I-MISS) content development

The content will be developed based on extensive literature review and expert consultations. Experts from the field of public health, medical doctor, epidemiologist, social scientist and waste management researchers, providers from municipality involved in solid waste management and NGOs will be included in expert consultations. Textual and content analysis will be conducted for the qualitative data. Themes and sub themes emerged will be pinned under the framework suggested in the motivation-opportunity-ability-behavior (MOAB) model [30–33]. The model explains that beliefs, evaluation of outcomes and social norms bring in the attitude towards the targeted pro environmental behaviour (In this case waste segregation), into what is collectively called the Motivation box. The intention for the target behaviour is the immediate antecedent for the behaviour/action in this model. Elements like ability and opportunity, will be considered as moderators to convert intention into action. The model also establishes a return connection between behaviour and belief directly or via ability which shows that when behaviour becomes a habit, the belief and evaluation of outcomes of thisbehaviour can be changed towards stronger attitudes [31–33].

The intervention content will include comprehensive information about types of household waste, correct waste segregation procedure, residents’ role and responsibilities, waste segregation and management and its impact on health, environment and wellbeing informed by the above consultation. The content will be organized so that volunteers will be able to deliver the I-MISS intervention in approximately 15–30 min per household session. The face and content validity of the developed intervention will be assessed. The intervention will be piloted in settings similar to the intervention areaswithin the Ujjain Municipal Corporation.

### Blinding

As the intervention consists of training that targets a change in behaviour, blinding of the study participants and investigators is not possible. However, the study team responsible for conducting outcome assessments will be blinded in terms of the households’ allotted groups and the participants will be requested to not discuss their allocation with the research team responsible for conducting follow-up assessments in order to minimize bias.

### Allocation concealment

The sampling procedure and randomization of wards will be performed by an external statistician. The list of selected wards will be communicated to the study investigators to initiate line listing, recruitment and baseline survey. However, at this stage the allocation of wards to intervention/control group will be concealed (by sealed envelope) by the external statistician. Allocation will be revealed after the baseline survey and before the initiation of intervention.

### Study measures

#### Primary outcome measures

Comparison of change in proportion of households practising waste segregation at different time points in the study when compared to baseline, between the intervention and control groups (Difference in differences between the groups). This is a categorical self-reported variable assessed at household level which will be captured by the waste segregation knowledge and behaviour questionnaire. The variable will reflect whether or not the household is segregating solid waste at household level, but will not reflect the accuracy of segregation.Comparison of change in proportion of mis-sorted waste at different time points in the study when compared to baseline between the intervention and control groups (Difference in differences between the groups). This variable will be objectively assessed at group level across intervention and control group by standard waste composition analysis (pick analysis). This variable will reflect the accuracy of waste segregation practices at group level.

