### Study design

This is an 18 month two-group parallel, c-RCT. The trial will be conducted following the Consolidated Standards of Reporting Trials (CONSORT)- extension for c-RCT guidelines [23]. The protocol is prepared in agreement with the standard protocol Items from the recommendations for interventional trials (SPIRIT) guidelines [24]. In our study, we will randomize at ward level i.e., wards will be our cluster randomization unit. Wards are the last administrative unit of municipality. The wards will be stratified into four stratum based on the percentage of slum population within a ward. From each stratum, wards will be randomized into intervention and control arms with 1:1 allocation ratio. The study design and trial flow are depicted in Fig. 1.

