##### Sample size

The sample size will be based on the differences in proportion, assuming that 50% households segregate waste in both groups. As we could not find previous literature quantifying the effect of similar kind of intervention in Indian setting, we assumed that in our study the intervention will increase the waste segregation practice in the intervention group by 20% compared to the control group. Given a 5% significance level and 80% power, then the minimum sample size is *n* = 184 per group. Assuming a design effect of 2 to adjust for the clustering effect, with 10% non-response rate and 20% loss to follow-up, the final sample size for each arm will be 425 households (total 850 households).

We have fixed the cluster number as eight. As the required sample size is 850 households, we will recruit 850 households from 8 wards i.e., around 110 households (cluster size) will be recruited from each ward.

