### Assessments (Table 1)

Assessment will be conducted at four time points (baseline, midline, end line and post intervention) across the study period.
*Baseline: *At baseline, all the households (intervention and control group households) will be assessed for the following:
○ Waste composition assessment through pick analysis, which is a reliable and validated method to assess the composition of the waste generated at group level.○ General socio-demographic details and waste segregation knowledge and behaviour.Findings of waste composition at baseline will be shared with respective households and two dustbins will be provided to each household (intervention and control) with relevant information regarding waste segregation.*Midline: *At the halfway point of the intervention (6th month), waste composition analysis of all the households (intervention and control group households) will be conducted using the pick analysis method.*End line:* At the 12^th ^intervention month waste composition, waste segregation knowledge and behaviour will be assessed again using the same methods as in the baseline assessment.*Post Intervention ***:** Waste composition, waste segregation knowledge and behaviour will be assessed finally at the 18 month mark (6 months after intervention completion). Feedback about the intervention will be collected from participants at this assessment.

**Table 1 Tab1:** Assessment plan

Time Point	Baseline (M-0)		Intervention period (12 Months)				Post Intervention (M-18)	
			Midline (M-6)		End line (M-12)			
Study tools	Intervention	Control	Intervention	Control	Intervention	Control	Intervention	Control
Socio-demographic	X	X	–	–	–	–	–	–
Waste composition analysis	X	X	X	X	X	X	X	X
Knowledge and behaviour, about waste segregation	X	X	–	–	X	X	X	X

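### Two primary outcomes over several follow-ups, with no primary time point and no rule for combining them: the chance of a false primary claim is about 10% to 23%, not 5%, if any one result counts

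*Protocol article*

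**What the plan says.** The section on primary outcome measures lists two outcomes, each a difference in differences between the arms.

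- Self-reported segregation by household, from the questionnaire: "Comparison of change in proportion of households practising waste segregation at different time points in the study when compared to baseline".
- Mis-sorted waste, measured objectively at group level by pick analysis: "Comparison of change in proportion of mis-sorted waste at different time points in the study when compared to baseline".

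Neither entry names a visit. The abstract is no narrower, since it refers only to the study period as a whole.

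The visits follow from the section Assessments (Table 1). Month 6 has pick analysis only: "At the halfway point of the intervention (6th month), waste composition analysis of all the households". Table 1 shows no questionnaire at that visit. Months 12 and 18 have both tools, and month 18 falls six months after the intervention ends.

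The sample size section works at one level, "Given a 5% significance level and 80% power", on one outcome, the share of households that segregate: "assuming that 50% households segregate waste in both groups", with the assumption that "the intervention will increase the waste segregation practice in the intervention group by 20% compared to the control group". It names no visit and does not mention mis-sorted waste.

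The analysis text is in the section Database management. It plans repeated-measures and factorial ANOVA for means, followed directly by a Bonferroni post hoc test. It then plans multilevel models and GEE to compare proportions between the arms over the study, with no adjustment mentioned. It gives no hierarchy, alpha split or success rule for the two primary outcomes.

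**The concern.** A 5% significance level describes the trial's primary claim only if it is clear which result makes that claim. Here two outcomes and up to five outcome-by-visit comparisons carry the word primary, and nothing says what pattern of results counts as success.

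The visits do not ask the same question. The hypothesis concerns fortnightly delivery for 12 months, which month 12 tests at the end of delivery. Month 18 tests whether a change lasts once the volunteers stop.

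The outcomes also differ in their exposure to bias. The first is reported by households that know their arm, and the article's methodological considerations concede that this could exaggerate differences. The second is measured objectively. With no decision rule, a positive self-report at one visit could stand as the primary result although the objective measure shows nothing.

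**Working it through.** **Inputs.** Significance level 5% and power 80% (Sample size). The level per test is inferred from that section, because the analysis text gives none. The number of sides is not stated; two-sided is assumed. The visit counts come from Table 1. Each test is taken as valid at its nominal level.

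**The plan's own figure.** The article states no familywise error, so there is none to reproduce. Its sample size is 184 per group before inflation. For 50% against 70%, two-sided 5% and 80% power, the usual two-proportion formula gives 93 per group; for 50% against 60% it gives 388. Neither is 184 (2 × 93 = 186 comes close). This is a separate matter and does not enter the error rates below.

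**Number of comparisons.** Self-reported segregation has 2 (months 12 and 18) and mis-sorted waste has 3 (months 6, 12 and 18). Total 2 + 3 = 5.

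**Familywise error if any one significant result counts as success.** For independent tests at levels a1, …, ak the rate is 1 − (1 − a1) × … × (1 − ak).

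- One longitudinal test per outcome, each at 5%: 1 − 0.95² = 9.75%.
- Bonferroni within each outcome (2.5% twice, 5%/3 three times): 1 − 0.975² × 0.98333³ = 1 − 0.9506 × 0.9508 = 9.6%.
- Bonferroni on the three pick-analysis visits only: 1 − 0.95² × 0.98333³ = 1 − 0.9025 × 0.9508 = 14.2%.
- Five uncorrected tests: 1 − 0.95⁵ = 22.6%.

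For two-sided, jointly normal test statistics, correlation cannot raise the last figure above 22.6%. Without any distributional assumption the bound is 5 × 5% = 25%.

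**Effect of correlation on five uncorrected tests.** Changes at two visits share a baseline. With equal variances and equal correlation r between visits, the covariance of the two changes is proportional to 1 − r and each variance to 2(1 − r), so their correlation is 0.5. The values below are assumptions, because the article gives none (simulation, 1,000,000 draws):

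| Correlation within outcome | Between outcomes | Familywise error |
|---|---|---|
| 0.5 | 0 | 20.5% |
| 0.5 | 0.3 | 19.7% |
| 0.7 | 0.3 | 17.7% |
| 0.8 | 0.5 | 15.4% |
| 0.9 | 0.7 | 12.4% |

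**After a fix.** With one time point and either outcome sufficient at 5% each, the rate is still up to 9.75%. With Holm or a fixed sequence across the two, or with both required, it is at most 5%.

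**Power cost of the split.** At 50% against 70%, testing at 2.5% (the stricter Holm step) raises the need from 93 to 113 per group. With 93, power falls from 80.0% to 71.0%. The planned 425 per arm, reduced by the plan's own allowances ("Assuming a design effect of 2 to adjust for the clustering effect, with 10% non-response rate and 20% loss to follow-up"), is worth 425 × 0.9 × 0.8 / 2 = 153 per arm. That gives 95.0% power at 5% and 91.3% at 2.5%, if the design effect of 2 and the 20-point difference hold.

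**The case against.** **The 23% is an extreme case.** A reader might infer that the protocol plans five separate tests at 5% and so carries a 23% error rate. The text does not say that. The 5% stands only in the sample size section, and the abstract and the multilevel/GEE sentence both fit one longitudinal comparison per outcome. Reaching 22.6% needs five separate, uncorrected, independent tests, any one of them sufficient. Independence is implausible when visits share wards and a baseline. This stands, so the figure is an upper end.

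**The Bonferroni sentence may help.** Mis-sorted waste is a proportion measured on groups, and it could be analysed as a mean by the factorial ANOVA that this sentence follows. This also stands, and it gives the 14.2% and 9.6% readings. On neither are the two outcomes controlled jointly.

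**Power.** It is tempting to say that the 80% attaches to nothing. That goes too far: the sample size section ties it to self-reported segregation. What is missing is the visit, and any power for mis-sorted waste.

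**Month 12 is not dictated.** The 12 months in the hypothesis describe how long the intervention is delivered. The background calls lasting change the hardest part, and the trial runs 18 months, so month 18 can be defended. The defect is that no choice is made.

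**Free choice of result.** A reader might infer that any one of the five results may be picked as primary. Each outcome is defined over all its visits, so picking one would depart from the definition. The definition still gives no rule for a mixed pattern.

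**The analysis plan may settle it.** The details of a multiplicity procedure are commonly left to a statistical analysis plan, which is not shown. That answers the choice between Holm and a sequence. It does not answer the primary definition, which the article does fix, as all follow-ups for both outcomes.

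**Conclusion.** The point holds. The article defines two primary outcomes over every follow-up, with no primary time point and no joint success rule, beside a sample size built on one outcome at a single 5% level.

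If any one significant result counts as success, the familywise error is about 10% on the more favourable readings of the analysis text, about 14% if Bonferroni reaches only the pick-analysis visits, and at most about 23% with five independent uncorrected tests. Under the assumed positive correlations the last figure is about 12% to 21%.

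These figures rest on an inferred two-sided 5% per test, on tests that are valid singly, and on success through either outcome. If both outcomes were required at one fixed visit, there would be no inflation, but the article does not say so. The 80% power applies to self-reported segregation at an unspecified visit only.

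The point should be corrected before analysis. It does not undermine the data collection.

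**What to change.** - Name one primary time point for both outcomes. Month 12, the end of the 12-month intervention in the hypothesis, is the natural choice; month 18 is possible if persistence is the main question.
- Control the two outcomes at 5% by Holm or by a fixed sequence stated in advance, or state that both must be significant.
- Make the other visits secondary: month 6 as early effect and month 18 as persistence.
- State that the sample size refers to self-reported segregation at the chosen time point.

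This takes a few sentences in the outcome, sample size and analysis sections and no extra data. With month 12 primary, the month 18 results become secondary. Holm costs some power per outcome, as worked out above. A fixed sequence keeps the full 5% for whichever outcome comes first, but no claim can be made on the second if the first fails. Requiring both outcomes needs no split, but success then depends also on mis-sorted waste, for which no power is stated.

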### Database management

The principal investigator will oversee the process of data management. REDCap will be used for database management. Participants will be given a unique participation information number (PIN) to ensure anonymity and data confidentiality. The entered data will be analysed using to appropriate statistical software. Descriptive statistics will include the mean, median, standard deviation and Interquartile range to summarize the numerical variables. Frequencies and percentages will be used for the categorical variables. Student t test will be used to compare means between the groups and chi square test will be used to compare the percentages between the groups. For skewed data, appropriate non parametric tests will be used. ANOVA repeated measures will be used to compare the means across the study periods (multiple time points) within the groups. Factorial ANOVA will be used to compare the means between the groups across the study period (multiple time points). Appropriate post hoc test (Bonferroni test) will be applied. Multi-level modelling (MLM) and Generalized Estimating Equation (GEE) will be done to adjust the clustering effect and to compare the proportions between the groups across the study period. Intention-to-treat analyses will be followed to assess interventions’ effectiveness.

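### The difference-in-differences primary contrast is valid, but a common-baseline model would estimate the same effect more precisely from data already collected

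*Protocol article*

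**What the plan says.** Under Primary outcome measures, the Protocol article defines two primary outcomes: self-reported household segregation (yes or no) and the proportion of mis-sorted waste from pick analysis, assessed at group level. Each is a change from baseline compared between arms, and each carries the label "Difference in differences between the groups".

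Both are measured at baseline in both arms (Assessments, Table 1). Pick analysis follows at 6, 12 and 18 months, and the questionnaire at 12 and 18 months. Under Allocation concealment: "Allocation will be revealed after the baseline survey and before the initiation of intervention".

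Database management plans multi-level modelling and GEE to handle clustering and compare proportions between arms over the study, with factorial ANOVA for means. It mentions neither a baseline mean shared by the arms nor baseline as a covariate.

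Under Sample size, "The sample size will be based on the differences in proportion", "assuming that 50% households segregate waste in both groups", with the effect given as "the intervention will increase the waste segregation practice in the intervention group by 20% compared to the control group". No baseline variance or baseline/follow-up correlation is given.

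**The concern.** A difference in differences subtracts the full baseline difference between arms. Under randomisation that difference is pure noise: wards are allocated by lottery, and the baseline is taken before the allocation is known, so both arms have the same expected baseline. Subtracting all of it is optimal only when baseline and follow-up are perfectly correlated. At any lower correlation, a smaller weight on the baseline gives the same target with less variance.

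At stake is precision, not validity. The trial fixes eight wards, four per arm, and so has little precision to spare. The baseline data needed to recover some of it are already being collected.

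**Working it through.** **1. The plan's own figure.** For 50% vs 70% (reading the 20% as points), two-sided 5%, 80% power:

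n = [1.96·√(2·0.6·0.4) + 0.84·√(0.25 + 0.21)]² / 0.2² = 93 per group.

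The plan states 184 per group. That is close to the two-arm total (2 × 93 = 186). It is also close to a per-group n for a difference in differences with zero correlation: 7.85 × (3 × 0.25 + 0.21) / 0.04 = 188.4, so 189. The figure therefore does not reveal which contrast was powered.

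**2. Theory, with variance components known.** Let r be the baseline/follow-up correlation of ward means. Variances relative to a follow-up-only comparison are:

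- difference in differences: 2(1 − r)
- common-baseline model: 1 − r²
- ratio of the first to the second: 2/(1 + r), which exceeds 1 for every r below 1.

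**3. Plausible r.** Inputs:

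- ICC: a design effect of 2 at 110 households per ward implies 1/109 ≈ 0.009. An ICC of 0.05 is an assumed alternative.
- Households analysed per ward: m = 110 × 0.8 = 88 (20% loss to follow-up).
- Household correlation 0.3 and ward autocorrelation (CAC) 0.5 to 0.9: assumptions, as the documents give neither.

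r = [ICC·CAC + 0.3(1 − ICC)/m] / [ICC + (1 − ICC)/m]

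| ICC | CAC | r | 2/(1 + r) |
|---|---|---|---|
| 0.009 | 0.5 | 0.39 | 1.44 |
| 0.009 | 0.8 | 0.52 | 1.31 |
| 0.009 | 0.9 | 0.57 | 1.28 |
| 0.05 | 0.8 | 0.71 | 1.17 |
| 0.05 | 0.9 | 0.79 | 1.12 |

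**4. Components estimated from eight wards.** The common-baseline mixed model was simulated with REML: 4 vs 4 wards, 88 households each, continuous outcome, one follow-up, 1,500 runs per cell. Variance of difference in differences divided by that of the model:

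| ICC | CAC 0.5 | CAC 0.8 | CAC 0.9 |
|---|---|---|---|
| 0.009 | 1.37 | 1.19 | 1.22 |
| 0.02 | 1.29 | 1.18 | 1.06 |
| 0.05 | 1.19 | 1.09 | 1.01 |

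Further simulation of the same model gave ratios of 1.01 to 1.45. With 6 ward-based degrees of freedom, mean intervals were narrower than for difference in differences and coverage was 95–98%. The top value, 1.45, sits at the theoretical 1.44 for CAC 0.5, so it should be read as the ceiling. On the standard-error scale, 1.2 to 1.45 means √1.2 = 1.10 to √1.45 = 1.20.

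**5. Degrees of freedom.** With pair fixed effects, 8 − 4 − 1 = 3 degrees of freedom remain (t = 3.18). Without them there are 6 (t = 2.45). (3.18/2.45)² ≈ 1.7, which exceeds the largest variance gain above.

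**The case against.** The strongest reply is that nothing here is wrong. Difference in differences is unbiased under randomised, concealed allocation. The multi-level model that is planned does not exclude a common baseline mean, and that detail could sit in an analysis plan not shown. This stands as far as it goes: the point is one of efficiency, and it is an inference that the contrast will be left unadjusted. But the article does name the contrast, for both primary outcomes, and a model with free arm-by-visit terms would reproduce it.

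Second, eight wards are few for estimating ward variance components. In a simulation with pair fixed effects, a ward component was at or near zero in 23–74% of fits. The variance ratio was 1.20 (ICC 0.009, CAC 0.9), 1.07 (ICC 0.05, CAC 0.9) and 1.00 (the same with household correlation 0.6). Ordinary ANCOVA on eight ward means can do worse than difference in differences: relative variances were 0.64 vs 0.60 at r = 0.7. So the gain shrinks and depends on the estimator, but for the mixed model it did not reverse. The pair-effects part of the objection also stands, and the fix allows for it.

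Third, a logit model with random effects would change the scale of the binary outcome. This too stands and is met in the fix.

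A reader might infer that power falls well below the planned 80%. At an assumed household correlation of 0.3, the variance relative to a single-time comparison is 1.46, which would turn a nominal 80% into 64%. The documents do not support that. They give no correlation, above about 0.5 difference in differences beats the single-time comparison, and the stated 184 does not reproduce as a single-time n. For the same reason it cannot be asserted that the sample size was computed for a single-time comparison.

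**Conclusion.** The point holds as an efficiency improvement. The stated primary contrast is valid and unbiased, but a common-baseline model targets the same effect with lower or, at worst, about equal variance from data already collected. The likely variance ratio is about 1.2 to 1.45 if the ICC is near that implied by the plan's design effect. It falls to about 1.0 to 1.1 at an ICC of 0.05 with ward autocorrelation of 0.8 to 0.9.

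These figures rest on an assumed household correlation of 0.3, an assumed ward autocorrelation, a continuous outcome and one follow-up. None was derived for mis-sorted waste, so for that outcome only the direction of the argument carries over. No bias and no specific loss of power is shown. On power, the Sample size section is only unclear about which contrast its figure describes.

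**What to change.** In the analysis text, keep the between-arm difference in change as the question and name its estimator:

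- a multi-level model with all visits as outcomes, one baseline mean for both arms, and arm-by-visit effects at each follow-up where the outcome is measured;
- random ward, ward-by-visit and household effects, with the 22-household block in place of household for mis-sorted waste (reading group level as that block);
- ward-based degrees of freedom, without requiring pair fixed effects if they use up the few available;
- the binary outcome reported as a difference in proportions, through an identity link or standardisation;
- the unadjusted difference in differences as a sensitivity analysis.

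In the Sample size section, state which contrast the power figure describes and, if it is the change from baseline, the correlation assumed.

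The cost is wording only, with no new data. The small downside is that ward variance components rest on eight wards, so part of the theoretical gain is lost. The choice should be fixed before outcome data are seen by arm.

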### Sampling strategy

The Ujjain Municipal Corporation is divided into 54 wards. Wards are the last administrative unit of the municipality. Wards will be our randomization unit (cluster).

All the wards in Ujjain Municipal Corporation (*n* = 54) will be chronologically arranged according to percentage of slum population in each ward. The consecutive wards will be arranged into pairs (*n* = 27 ward pairs). These pairs will be divided into quartiles based on the percentage of slum population. One ward pair will be selected by simple random sampling from each quartile. Thus, a total of four ward pairs (eight wards) will be selected. The lottery method (simple randomization) will be used to randomly allocate wards in each pair into intervention and control groups.

A survey team will conduct a preliminary door to door survey to list the total number of households in the selected eight wards. They will gather information of slum and non-slum households. Thus, at the end of this process, we will have a sampling frame (line listing of households classified as slum and non-slum areas).

After the household listing, each ward (cluster) will be divided into groups of 22 consecutive households. To meet the required sample size, we will identify at least five groups of 22 households from each ward (5X22 = 110 households). In total, 440 households will be recruited for the intervention group and another 440 for the control group.

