### Study tools

*Pick analysis (waste composition assessment): *Pick analysis is a method to characterize the content of a waste stream. This analysis aims to estimate the waste generation per capita per time and to analyse waste segregation behaviour where waste fractions were sorted correctly based on the recycling schemes. This method can measure the actual waste sorting behaviour at household/community level. The method was developed and validated by Dahlén and Lagerkvist [34] and is a recommended method by Swedish Waste Management Association [35](2013). Rousta et al. (2016) have implemented this method to create RBT procedure (Recycling behaviour Transition) to design and assess the interventions of increasing the recycling rate of a community in a medium-sized city [31]. A pre- designed proforma to capture the quantity and composition of the waste generated at group level will be used.*Waste segregation knowledge, behaviour questionnaire***:** Based on the literature [11, 13, 22, 36–41] and experts’ consultation, the research team has developed an extensive questionnaire to assess the awareness, attitude and behaviour related to household level waste segregation. This questionnaire will be used to assess the belief, social norms, knowledge, ability, motivation factors, opportunity and practices about waste segregation study household members. One section of the questionnaire will capture socio-demographic details of the study households.*Intervention log-book (Volunteer log book):* A pre-designed log book will be used by the volunteers to monitor the attendance of household members present during intervention and any other information shared by household members.

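### The protocol does not say which unit mis-sorted waste, the second primary outcome, is measured on, and the stated power and several listed tests do not fit it

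*Protocol article*

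**What the plan says.** The protocol article names two primary outcomes. The first is whether a household reports that it segregates waste. The second is the proportion of mis-sorted waste, of which Primary outcome measures says: "This variable will be objectively assessed at group level across intervention and control group by standard waste composition analysis (pick analysis".

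Two further places repeat the level. Study tools: "A pre- designed proforma to capture the quantity and composition of the waste generated at group level will be used". Assessments calls pick analysis a method "which is a reliable and validated method to assess the composition of the waste generated at group level". Study tools also says "This method can measure the actual waste sorting behaviour at household/community level", which describes what the method is able to do rather than how data will be recorded here.

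Sampling strategy gives the word *group* a second meaning: "each ward (cluster) will be divided into groups of 22 consecutive households", and then "we will identify at least five groups of 22 households from each ward (5X22 = 110 households". Elsewhere, including in Primary outcome measures, *group* means the intervention or control arm.

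Sample size rests on one endpoint: "The sample size will be based on the differences in proportion, assuming that 50% households segregate waste in both groups". The analysis paragraph (under Database management) lists the t test for means, chi-square for percentages, factorial ANOVA for means between arms over time, and multi-level modelling (MLM) and GEE for proportions with clustering. It does not say which of these is meant for mis-sorted waste.

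**The concern.** This is the only objective primary outcome. The other is self-reported, is stated not to reflect accuracy of segregation, and comes from participants who know their allocation. Mis-sorted waste therefore carries much of the trial's evidential weight.

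Three things are at stake.

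- **Unit.** If waste is combined across an arm before weighing, no between-unit variation remains and no later analysis can recover it.
- **Power.** The 80% power statement and the claim of adequate sample size (Methodological Considerations) read as covering the trial, but no input to the calculation concerns mis-sorted waste.
- **Test.** The outcome is called a proportion, which points a reader to chi-square. It is a ratio of masses, not a count of households. The t test and factorial ANOVA, as listed, take no account of wards and would give standard errors that are too small.

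**Working it through.** **The plan's own figure.** The inputs are 50% segregating, a 20% increase, 5% significance and 80% power. For 50% against 70%, two-sided, the pooled two-proportion formula gives 93 per group (186 in total). The stated 184 per group is close to that total. For 50% against 60% it gives 388 per group. With design effect 2, 184 × 2 = 368, and 368/(0.9 × 0.8) = 511, not 425. That mismatch is a separate matter. What counts here is that every input describes the household proportion; there is no SD, effect size or number of units for mis-sorted waste.

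**Number of values per arm at each time point.** Inputs from Sampling strategy: 440 households per arm, groups of 22, five groups per ward, 8 wards in 4 pairs.

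| Reading of *group* | Values per arm | Consequence |
|---|---|---|
| 22-household block | 440/22 = 5 × 4 = 20 | analysable, nested in 4 wards |
| Ward | 4 | analysable on ward values |
| Trial arm | 1 | no valid standard error |

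The article asks for at least five blocks per ward, but the target of 440 households per arm caps the count at 20.

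**Detectable difference with 20 blocks per arm.** Let SD be the block-level SD of the analysed value and ρ the within-ward correlation. With five blocks per ward, the variance of the arm difference is 2 SD² (1 + 4ρ)/20. Degrees of freedom are 8 − 2 = 6 if wards are treated as unpaired, and 4 − 1 = 3 if the pairs are respected. By the noncentral t, two-sided 5% and 80% power need a difference of about 3.37 standard errors on 6 df and 4.26 on 3 df. The ρ values are assumed.

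| ρ | √(2(1 + 4ρ)/20) | 6 df | 3 df |
|---|---|---|---|
| 0 | 0.316 | 1.06 SD | 1.35 SD |
| 0.1 | 0.374 | 1.26 SD | 1.59 SD |
| 0.3 | 0.469 | 1.58 SD | 2.00 SD |

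With ward values only (4 per arm), the figures are 2.38 ward-level SD on 6 df and 3.01 on 3 df.

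**In percentage points.** For assumed SDs of change, with ρ from 0 to 0.3:

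| SD of change | 6 df | 3 df |
|---|---|---|
| 5 points | 5.3 to 7.9 | 6.7 to 10.0 |
| 10 points | 10.6 to 15.8 | 13.5 to 20.0 |
| 20 points | 21.3 to 31.6 | 26.9 to 39.9 |

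**Ignoring wards.** An ordinary t test on 20 blocks per arm (38 df) was simulated with no true effect and five blocks per ward. At a nominal 5%, the type I error was about 7.5%, 10% and 19 to 20% for ρ of 0.05, 0.1 and 0.3.

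**The case against.** The natural reading of the outcome definition is blocks spread over the two arms, since the block is the only subdivision defined below the ward. Nowhere does the article say that waste will be pooled by arm. This is fair: pooling by arm is a reading that the wording permits, not a stated plan. But the same definition also uses *group* for the arm, and the choice cannot be reversed after weighing.

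The choice of model may sit in an analysis plan that is not shown. That also stands, and a missing model specification alone would be no finding. However, the article does list tests, and several of them would mislead if applied to this outcome. The measurement unit and the basis of the power statement belong in the protocol.

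Three stronger readings are tempting and are not supported.

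- **MLM and GEE cannot be used.** They can, if the fraction is modelled as continuous with ward clustering and small-sample handling for 8 wards.
- **The outcome is shown to be underpowered.** It is not. The documents give no SD or within-ward correlation. With an SD of change of 5 points, 20 blocks per arm have at least 80% power for 10 points at every correlation tried. The figures in SD units are for a single comparison and take no credit for baseline adjustment or repeated measurement.
- **The feedback sentence contradicts group-level measurement.** Assessments says "Findings of waste composition at baseline will be shared with respective households". Giving each household its own block's result satisfies this, so no contradiction follows.

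**Conclusion.** The concern holds in this form. The article fixes a primary outcome at a level that it does not define unambiguously. The number of values per arm at each time point is 20 at most, 4 if the ward is meant, and 1, with no valid test, if the arm is meant. The stated 80% power and sample size say nothing about this outcome. Of the listed methods, chi-square does not suit it, the t test and factorial ANOVA would understate the standard error, and MLM or GEE are usable with the conditions above.

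The size depends on assumed quantities: 1.06 to 1.58 SD detectable on 6 df, or 1.35 to 2.00 SD on 3 df, for ward correlations of 0 to 0.3. Two further assumptions are that the proportion is by mass, as the weighing of quantity in pick analysis implies, and that all 20 blocks per arm supply data. Power may be good or poor; the article gives no basis for saying which.

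**What to change.** 1. In Primary outcome measures and Study tools, state that waste is collected, weighed and recorded separately for each 22-household block, and never pooled by arm.
2. In the analysis paragraph, name one method for this outcome in place of chi-square, t test or factorial ANOVA. It could be a linear mixed model on the block fraction (blocks within wards, adjusted for the baseline fraction, small-sample degrees of freedom), or an analysis of ward-level changes that respects the ward pairs.
3. In Sample size, say that the 80% power applies to the first primary outcome only. Give a detectable difference for the second under a stated SD and within-ward correlation, marked as assumptions.

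The cost is labelling waste by block during collection, some protocol wording, and a stated precision that looks less favourable. Neither the number of households nor the number of wards changes.
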